#### Focus Groups

Workshop facilitators, organizational leadership, and workshop participants were invited to participate in separate virtual focus groups via email. Focus group participants participated in the group virtually using WebEx (Cisco Systems, Inc), a secure, web-based videoconference platform. The focus groups were recorded, transcribed verbatim, and anonymized. Focus group participants received honoraria in the form of a CAD $50 (US $35.74) e-gift card following their participation.

### Statistical Analysis

#### Quantitative Analysis

To evaluate reach, we will examine the number, attendance, and demographic profiles of participants at each site. To evaluate effectiveness and maintenance of the intervention, we will assess changes in outcome measures (21-item Depression, Anxiety and Stress Scale; Parenting Stress Index, 4th Edition; Brief Family Distress Scale; Multi-System Model of Resilience Inventory; Short Warwick–Edinburgh Mental Well-being Scale; and Patient Health Questionnaire-4) and ACT process measures (Cognitive Fusion Questionnaire, Valued Living Questionnaire, and Acceptance and Action Questionnaire-II) across 3 time points (before workshop, after workshop, and follow-up). We will first conduct a within-subjects repeated measures ANOVA, checking assumptions of normality (via skewness and kurtosis *z* values) and the absence of outliers (via boxplots). Where significant main effects are found, we will perform Bonferroni-adjusted pairwise comparisons (pretest-posttest, before follow-up, and after follow-up). In addition, we will use mixed-effects modeling to account for repeated measures within individuals and variability across study sites, and to examine potential predictors and moderators (eg, delivery modality, group composition, and demographic variables). Subgroup analyses will be stratified by gender identity, age, racial or ethnic identity, and living situation, exploring both the main effects and interactions. Missing data will be addressed according to the intention-to-treat principle, using multiple imputation in SPSS (IBM Corp) with all demographic and baseline outcome variables included as predictors.

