### Research Objectives

The aim of this study is to evaluate the community implementation of the Caring for the Caregiver ACT (CC-ACT) model, designed to enhance the mental health and resilience of caregivers of individuals with NDDs, co-delivered by caregiver-clinician facilitation teams. Our research objectives and questions are presented in Textbox 1.

Research objectives and questions.Evaluate the implementation of a caregiver and clinician-partnered Caring for the Caregiver Acceptance and Commitment Training (CC-ACT) workshop delivered in communities across Canada to support the mental health and resilience of caregivers of individuals with neurodevelopmental disabilities.Is it feasible to recruit caregiver participants across study sites, and what proportion of participants complete the workshop?Does the workshop lead to enhanced mental health and resilience in participants, and is this change maintained at follow-up?What demographic, clinical, and organizational variables predict or moderate change, for example, whether the workshop is delivered to a mixed or homogeneous disability caregiver group, delivered in-person or virtually, or to caregivers of children or young adults?How is the workshop perceived by various community groups, including participants, clinician facilitators, caregiver facilitators, and organizational leaders?What adaptations become necessary as the workshop is implemented in various real-world settings?What is the long-term sustainability of the workshop program in terms of its resource use, time, and potential for wide-scale adoption?Evaluate the unique collaboration between caregivers and clinicians codelivering the workshop.What are the facilitators and barriers to successful caregiver-clinician collaborations with regard to facilitator training and workshop delivery?What is the value of this collaboration from various community group perspectives, including participants, clinician facilitators, caregiver facilitators, organizational leaders, and the research team?

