### CC-ACT Workshop Description

Our workshop is a group intervention based on ACT, which aims to increase psychological flexibility through training in 6 core processes: defusion (relating to thoughts as merely thoughts), acceptance (willingness to experience thoughts and feelings rather than avoiding them), contact with the present moment (being in touch with the here and now rather than being stuck in the past or worrying about the future), self-as-context (being in contact with a transcendent sense of self rather than being stuck with self-labels), values (clarifying what gives life value and meaning), and committed action (persisting in value-guided actions). The intervention consists of experiential exercises, mindfulness practices, and small and large group reflective sharing [20].

Groups are guided by trained cofacilitators, including at least one clinician with experience in the NDD community and at least one family caregiver of an individual with an NDD. Each group can accommodate 10 to 15 participants. For in-person delivery, the workshop is delivered over 2 consecutive sessions, an evening session (3 h) and a full-day session (8 h), followed by a final evening session (3 h) 1 month later (Table 1; refer to Fung et al [20] for more details on intervention content). For virtual delivery, the workshop is conducted over 4 to 5 consecutive weekly 2-hour sessions, with an additional 2-hour session occurring 1 month later.

**Table 1 table1:** Overview of Caring for the Caregiver Acceptance and Commitment Training (CC-ACT) content across delivery modalities.

Virtual intervention (5 to 6 sessions; 2 h per session)	In-person intervention (3 sessions: S1 half-day [3 h], S2 full day [8 h], and S3 half-day [3 h])
S1: Overview of ACT (eg, hexaflex and hand gestures) Contact with the present moment exercise (eg, meditation with self-object, leaves on a stream)	S1: Overview of ACT (eg, hexaflex and hand gestures) Contact with the present moment exercise (eg, meditation with self-object and leaves on a stream)
S2: Acceptance exercise (eg, keeping the count)	S2: Acceptance exercise (eg, chair sculpture) Defusion exercise (eg, paired sharing) Values exercise (eg, values wordlist and 100th birthday) Committed action exercises (eg, bull’s eye and bus driver)
S3: Defusion exercise (eg, adventures of the pink elephant and our song)	—^a^

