#### Phase 2: Implementation

From 2022 to 2024, we partnered with 11 sites to deliver up to 2 ACT workshops per site, with each workshop targeting 10 to 15 caregiver participants. Sites across Canada included hospitals and community agencies providing services for children or families with NDDs (Table 2). Facilitators at each of the sites completed 20 hours of basic training from our team. Caregivers were eligible to participate in the workshops if they identified as a family caregiver (ie, parent, grandparent, or adult sibling) of someone with an NDD. Depending on the mandate of the host agency, workshops were held for caregivers of people of specific ages (ie, children, youth, or adults) or specific NDD diagnostic groups (ie, autism or FASD). Workshops were conducted in 2 waves (6-9 mo apart) to allow learnings from the first wave to inform the second and ensure adequate recruitment time.

**Table 2 table2:** Implementation sites.

Organization	Organization type	Province	Target population	Workshop format
1	Mental health hospital	Ontario	Two populations: caregivers of people aged >16 y with NDDs^a^ and fathers of people aged >16y with NDDs	5-wk virtual
2	Community health center	Ontario	Caregivers of children, youth, and adults with NDDs	5-wk virtual
3	Nonprofit organization: IDD^b^	Ontario	Caregivers of children, youth, and adults with NDDs	6-wk virtual
4	Nonprofit organization: sibling disabilities	Canada	Adult sibling caregivers of people with NDDs	6-wk virtual
5	Rehabilitation hospital	Ontario	Caregivers of children and youth with disabilities and complex health conditions	6-wk virtual
6	Nonprofit organization: disabilities	British Columbia	Caregivers of children and youth with NDDs and complex health conditions in early intervention and school-age programs	6-wk virtual
7	Nonprofit organization: disabilities	Ontario	Caregivers of children and youth with NDDs	6-wk virtual
8	Nonprofit organization: IDD	Quebec	Caregivers of children, youth, and adults with NDDs	6-wk virtual
9	Nonprofit organization: disabilities	Ontario	Caregivers of children, youth, and adults with NDDs	6-wk virtual
10	Nonprofit organization: developmental services	Ontario	Caregivers of individuals with fetal alcohol spectrum disorder	6-wk virtual
11	Community health center and nonprofit autism organization	Nova Scotia	Caregivers of people with autism	In-person

^a^NDD: neurodevelopmental disability.

^b^IDD: intellectual or developmental disability.

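### Delivery modality is a named moderator, but only one of the 11 sites delivered in person, so a modality effect cannot be told apart from that site

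*Protocol article*

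**What the plan says.** Textbox 1 (Research Objectives) asks which variables predict or moderate change and gives as examples "whether the workshop is delivered to a mixed or homogeneous disability caregiver group, delivered in-person or virtually". The Quantitative Analysis section carries this into the model. Mixed-effects modelling is to allow for repeated measures and between-site variability, and "to examine potential predictors and moderators (eg, delivery modality, group composition, and demographic variables".

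In Phase 2, the team reports that "we partnered with 11 sites to deliver up to 2 ACT workshops per site, with each workshop targeting 10 to 15 caregiver participants". Table 2 gives the format at each site: organizations 1 and 2 ran a 5-week virtual workshop, organizations 3 to 10 a 6-week virtual workshop, and organization 11 alone delivered in person. Organization 11 is described as "Community health center and nonprofit autism organization", in Nova Scotia, with target population "Caregivers of people with autism". The only other site defined by one diagnosis is organization 10, "Caregivers of individuals with fetal alcohol spectrum disorder", which is virtual.

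The CC-ACT Workshop Description sets out the in-person format as "an evening session (3 h) and a full-day session (8 h), followed by a final evening session (3 h) 1 month later" and the virtual format as "4 to 5 consecutive weekly 2-hour sessions, with an additional 2-hour session occurring 1 month later".

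Strengths and Limitations notes the lack of randomisation but not that in-person delivery rests on a single site.

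**The concern.** A moderator set at site level can be told apart from the sites only if each of its levels occurs at several sites. Here one level occurs once. Whatever is particular to organization 11, such as its region, its local facilitation team or its autism-specific group, would appear in the modality-by-time coefficient and could be reported as an effect of meeting in person. A null result could equally be read as virtual delivery doing as well. Recruiting more participants at the same sites would not have cured this. Data collection is complete, so no later document can add a second in-person site.

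**Working it through.** The article states no sample size or power figure, so there is none to reproduce. The consent percentage checks: 113/195 = 57.9%.

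**Is modality identifiable?** I coded Table 2 with one row per site.

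- In-person: 1 of 11 sites.
- Correlation of modality with Nova Scotia: 1.00. Correlation with an autism-specific target population: 1.00.
- Intercept, modality, Nova Scotia and autism target together: 4 columns, rank 2.
- Site as a fixed factor plus modality: 12 columns, rank 11, so modality is not estimable.
- With a random site effect the coefficient is estimable, but only by judging organization 11's departure against the spread among the virtual sites. There is no in-person replication with which to check that assumption.

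**Is composition in the same position?** Diagnosis-specific versus mixed is 2 sites (10 and 11) versus 9.

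- Correlation with modality 0.67, R² 0.45. Intercept, modality and composition have rank 3 of 3, so the two are separable.
- Variance factors, in units of the variance of one site mean with equal site sizes: modality alone 1 + 1/10 = 1.10; composition alone 1/2 + 1/9 = 0.61.
- With both in the model, modality becomes organization 11 versus 10 (1 + 1 = 2.00), and composition becomes organization 10 versus the nine mixed sites (1 + 1/9 = 1.11).

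**Contact hours.** In person 3 + 8 + 3 = 14 h. Virtual 4 × 2 + 2 = 10 h or 5 × 2 + 2 = 12 h. The ranges do not overlap, but hours also vary among virtual sites (R² with modality 0.45).

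**Illustrative precision.** Assumptions not in the article: two-sided alpha 0.05, 80% power, n in-person participants among the 113, the rest spread evenly over ten sites (m = (113 − n)/10), and site ICC of the change score ρ. In SD units of change:

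SE = √{ρ + (1 − ρ)/n + [ρ + (1 − ρ)/m]/10}

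The test uses t on 11 − 2 = 9 df (critical value 2.262). The noncentrality for 80% power is about 3.15, so the detectable difference is about 3.15 × SE.

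| n in person | ρ | SE | Detectable difference (SD) |
|---|---|---|---|
| 30 (2 × 15, the planned ceiling) | 0 | 0.213 | 0.67 |
| 113/11 = 10.3 (even spread) | 0 | 0.327 | 1.03 |
| 10.3 | 0.05 | 0.396 | 1.25 |
| 10.3 | 0.10 | 0.454 | 1.43 |
| 5 | 0.10 | 0.546 | 1.72 |

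With an even spread, power for an assumed difference of 0.5 SD is 28%, 20% and 17% at ρ = 0, 0.05 and 0.10.

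**The case against.** The best defence is that the wording is exploratory. The moderators are called potential and are given as examples, no modality p value is promised, and the predictors the Discussion expects to find are education, ethnicity and gender. Format was chosen to suit local needs, and the article already concedes that lack of randomisation limits causal inference. All of that is true and lowers the severity. It does not remove the problem: calling an analysis exploratory does not make its target identifiable, and the general caveat about randomisation does not tell a reader that one arm of the comparison is a single site.

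Several stronger readings are tempting, and the documents do not support them:

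- **Group composition is aliased too.** It is not. Organization 10 is diagnosis-specific and virtual, so composition and modality are separable. The contrast is thin, not confounded by construction.
- **Modality is fully confounded with diagnosis.** This holds for the site's target population only. The child's diagnosis is collected for each participant, and the broad NDD groups are not said to exclude autism.
- **Contact hours are a confounder.** They differ, but they are part of how each format is defined and so belong to the package being compared.
- **The modality term cannot be fitted at all.** That is so only with fixed site effects; with random site effects it can be fitted, at the price of an assumption that cannot be checked.
- **A false modality effect will reach the best-practice guidelines.** The guideline content listed in the Discussion does not single out modality, so this is conjecture.

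**Conclusion.** The point holds for delivery modality. As planned, its moderator effect is organization 11 against ten virtual sites and cannot be separated from that site's region, facilitators and target population. This follows from Table 2 alone and needs no assumed figure.

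Composition needs a caveat, not removal: it is a between-site contrast resting on organizations 10 and 11, and on organization 10 alone once modality is in the model.

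The precision figures, about 0.67 to 1.72 SD of change, are illustrative. They depend on the assumed in-person numbers (5 to 30), ICC (0 to 0.10), alpha and power, and on an even spread over the virtual sites. They are secondary, because the confounding would remain at any sample size.

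Severity is moderate. This is a secondary moderator question, and the main comparison of change before, after and at follow-up does not depend on it.

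**What to change.** - In Quantitative Analysis, take delivery modality out of the tested moderators. Report outcome change by delivery format descriptively, with confidence intervals and no interaction p value.
- In Textbox 1, reword the in-person or virtual part of the question so that it asks for a description of results by format.
- In Strengths and Limitations, state that in-person delivery rests on one site, which is also the only Nova Scotia site and the only autism-targeted one.
- Label any result on mixed versus diagnosis-specific groups as exploratory and resting on two sites.
- Optionally, repeat the time-effect analysis without organization 11 as a sensitivity check.

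The cost is wording and, if wanted, one extra run. Analysis was still under way in August 2025, so the change was practicable at that point. What is given up is a formal test of modality.

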#### Qualitative Analysis

The evaluation of all components of RE-AIM will also be undertaken using a qualitative approach. All qualitative data (focus groups, survey open-ended responses, and meeting notes) will be analyzed using descriptive content analysis [34]. This is a flexible approach that can be used to systematically summarize different types of qualitative data and is often used in applied research settings. Two team members will review the data and generate a codebook informed by the RE-AIM framework. Data will be independently coded, and reviewers will use a consensus. Several strategies will be used to establish trustworthiness for the qualitative components of this study, including credibility, dependability, transferability, and confirmability [35,36]. Data collection instruments (ie, focus group guide and open-ended survey questions) will be codeveloped by members of our multidisciplinary team, including caregivers and clinicians, to ensure they are clear, relevant, and easy to understand. We will create an environment in which participants feel comfortable expressing their opinions, including ensuring that focus groups are facilitated by an external individual who is not directly involved in delivering the intervention, and we will hold separate groups for caregivers, facilitators, and organizational leadership. An iterative coding process will be used based on multiple readings of the data and the perspectives of multiple team members. An audit trail will be used to clearly document each step of the analysis process. Thick description will be used in reporting to contextualize findings.

#### Data Management

Quantitative data were deidentified, and qualitative data were anonymized to safeguard participant confidentiality. Data are stored in a password-protected database on a secure computer network, accessible only to authorized research staff who will abide by the confidentiality regulations set by the Research Ethics Board. Each survey participant was assigned a unique ID number, which was used to link their data across all research activities and time points. The master list linking participant IDs to identifying information is stored in a separate, secure folder on the computer network.

Survey and focus group data are securely managed using a REDCap database designed and maintained for this study. Data are monitored and reviewed frequently by study investigators to ensure adherence to confidentiality protocols, Research Ethics Board guidelines, and protocol design. At the end of the study, all data will continue to be securely stored in compliance with institutional and regulatory requirements.

## Results

As of August 2025, data collection was complete, and we are analyzing data based on the protocol outlined earlier. Our CC-ACT workshops reached a total of 195 caregivers of individuals with NDDs, of whom 113 (57.9%) consented to participate in the research evaluation. Among these 113 participants, there were 4 (3.5%) dropouts or withdrawals from the study. In total, 3 focus groups were conducted, including 5 caregiver workshop participants, 13 facilitators, and 5 organizational leaders.

The team is in the middle of systematically analyzing these findings, with contributions from both researchers and individuals with lived experience. Qualitative survey and focus group data have undergone initial coding and are now being reviewed by the full team. Multiple data sources are being analyzed in parallel, each with dedicated leads: (1) RE-AIM framework implementation data; (2) participant outcome data, including self-reports and attendance records; (3) facilitator surveys and fidelity checklists; and (4) qualitative interview transcripts from caregivers, facilitators, and organizational leaders.

Our goal is to finalize all data analyses by the end of 2025, which will inform the preparation of best-practice guidelines (Table 4). Our analyses will help identify sociodemographic and process variables that moderate or mediate outcomes, helping to clarify the mechanisms contributing to improvements in psychological flexibility and resilience. Evaluation of the implementation processes using the RE-AIM framework will further illuminate the factors related to feasibility, acceptability, fidelity, adaptations, and resource use. These insights will help guide the broader adoption of the ACT intervention model across community settings.

**Table 4 table4:** Project timeline.

Project activities	2022	2023	2024	2025
Engage, train, coach, prepare, and support implementation teams	✓			
Ethics approval	✓			
Implement first set of workshops	✓			
Implement second set of workshops	✓	✓		
Implementation evaluation	✓	✓	✓	
Conduct focus groups		✓		
Data analysis and knowledge translation		✓	✓	✓
Knowledge Translation and Exchange (forums, conferences, website, publications, and toolkit)		✓	✓	✓

## Discussion

### Anticipated Findings

Previous studies, including our own work, support the efficacy of CC-ACT to support the mental well-being of caregivers. This study will be important as there is a lack of effective evidence-informed interventions for caregivers of people with NDDs in Canada, and even fewer that have been studied in real-world settings. A meta-analysis found that ACT has significant effects on depressive and anxiety symptoms, stress, and quality of life in caregivers of various chronic conditions such as dementia, chronic pain, asthma, multiple sclerosis, and neurodevelopmental conditions [37]. Findings from this study will help to elucidate the practical implementation of this evidence-informed intervention across diverse settings in Canada, which may also pave the way for scale-up for caregivers of other chronic conditions as well.

All participating sites have successfully recruited and completed their planned workshops. As we formally analyze the data, we anticipate that we will gather nuanced implementation experiences under the RE-AIM framework.

In terms of reach, we will examine the sites’ challenges and successes in recruiting caregivers. Analysis of parameters, such as the preferred time of the year for the workshops, will inform how best to organize and plan caregiver interventions in the future. Furthermore, analysis of the HEIA data, conducted in phase 1, will be valuable in identifying regional and contextualized equity and access barriers, such as ethnicity, gender, SES, and language.

Our earlier work demonstrated the overall efficacy of our workshops among caregivers of people with autism, as implemented in the context of a hospital-based research study [14,16,17]. We anticipate similar positive results with the current protocol. However, we anticipate that the degree of effectiveness may vary with implementation in real-world contexts, for example, due to population differences as well as implementation fidelity. Given the diversity of workshop participants across sites, we expect to be able to identify some predictors of effectiveness (eg, education, ethnicity, and gender) and to examine whether different ACT processes mediate outcomes across participant subgroups. Follow-up data may also shed light on the factors associated with the individual maintenance of ACT skills.

Our evaluation of the implementation across the 11 sites will help us explore and understand the balance between fidelity and adaptation. We anticipate that the workshop fidelity will generally be high, as our intervention exercises have built in flexibility, and we have offered customized coaching to the facilitation teams. Consistent with Lake et al [38], we anticipate that the complementary perspectives of caregiver and clinician facilitators can enhance the experience of facilitator teams as well as the workshop.

With the structure and support provided by the study, all sites successfully adopted the workshop model. We anticipate that the analysis of feedback from site facilitation teams and organizational leadership will reveal factors that facilitate or hinder adoption, as well as identify what is needed for long-term maintenance beyond the study period. Throughout the study, we systematically documented the implementation processes and contextual factors at the participating sites. They will be analyzed to identify common facilitators, barriers, and effective delivery strategies. Insights will be synthesized into a set of evidence-informed best-practice guidelines to support future community-based workshop implementation. These guidelines will include recommendations on facilitator training, participant engagement, cultural and contextual adaptations, and resource planning, with the aim of enhancing scalability, fidelity, and sustainability across diverse community settings.

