## Methods

### Implementation Science Framework: Reach, Effectiveness, Adoption, Implementation, and Maintenance

The study is guided by the reach, effectiveness or efficacy, adoption, implementation, and maintenance (RE-AIM) implementation science framework [19], providing an overarching structure to examine the processes and outcomes of the real-world implementation of evidence-based health workshops in 5 areas: reach, effectiveness, adoption, implementation, and maintenance. *Reach* is a measure of participation at the individual level, such as the number or characteristics of program participants. *Effectiveness* includes an assessment of the positive and negative outcomes of the program. *Adoption* examines the uptake at the individual or organizational level. *Implementation* examines the degree to which the program is conducted as intended in various real-world settings. *Maintenance* evaluates the extent to which the program impact is enduring at the individual and organizational levels.

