##### Project Evaluation Plan

The project is being evaluated using a mixed methods design to address the two primary research questions: (1) evaluation of CC-ACT intervention implementation using RE-AIM (Table 3) and (2) evaluation of caregiver-clinician collaboration (Textbox 3).

**Table 3 table3:** Implementation process evaluation.

RE-AIM^a^ dimensions	Evaluation indicators and data sources
Reach	Number of people who expressed interest, number of people who were recruited, number of people who completed, and % of completers Sociodemographic and other participant characteristics (eg, type of NDD^b^) comparisons: Cross-site comparisons
Effectiveness	Before versus after comparisons: outcome measures; process measures Analysis of moderators on outcome measures Mediational analysis of process measures on outcomes Estimated cost ranges for staff, materials, and other items necessary to run the workshops Perceived benefits from cross-site focus groups
Adoption	Perceived feasibility, acceptability, and fit from focus groups
Implementation	Fidelity checklists Health Equity Impact Assessment Postworkshop surveys completed by facilitators and CC-ACT^c^ peer coaches
Maintenance	Before versus after versus follow-up survey data and focus groups Tracking of agencies implementing regular programming based on our model

^a^RE-AIM: reach, effectiveness, adoption, implementation, and maintenance.

^b^NDD: neurodevelopmental disability.

^c^CC-ACT: Caring for the Caregiver Acceptance and Commitment Training.

Caregiver-clinician collaboration evaluation.

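### Adoption is defined as uptake, but its only indicator is focus-group perception, and the claim that all sites adopted covers only agencies that had already agreed to partner

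*Protocol article*

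**What the plan says.** The Implementation Science Framework section gives a working definition for each RE-AIM domain. Adoption "examines the uptake at the individual or organizational level". Maintenance "evaluates the extent to which the program impact is enduring at the individual and organizational levels".

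Table 3 (Project Evaluation Plan) then assigns indicators. Adoption has a single entry: "Perceived feasibility, acceptability, and fit from focus groups". Reach, in the same table, has explicit counts: people interested, recruited and completing, and the percentage of completers. Maintenance has survey data at three time points, focus groups, and tracking of agencies that run regular programming on the model.

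Phase 2: Implementation describes how sites took part: "we partnered with 11 sites to deliver up to 2 ACT workshops per site". It adds that "Facilitators at each of the sites completed 20 hours of basic training from our team", with coaching as needed. The article does not say how many agencies were approached or how partners were chosen.

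Anticipated Findings states: "With the structure and support provided by the study, all sites successfully adopted the workshop model". Textbox 1 (Research Objectives) asks: "What is the long-term sustainability of the workshop program in terms of its resource use, time, and potential for wide-scale adoption". In the Table 4 timeline, "Conduct focus groups" is ticked for 2023 only.

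**The concern.** The indicator does not match the construct. Agencies or facilitators could rate the workshop as feasible and acceptable and still not take it up, or take it up despite reservations. A focus-group summary cannot tell these cases apart.

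The one statement in the article that does read as an uptake result, in Anticipated Findings, is conditional on partnership. An agency that was approached and declined, if there was one, cannot appear in it.

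This matters because Textbox 1 asks about the potential for wide-scale adoption, and the Discussion says the findings will feed best-practice guidelines intended to support scaling. A reader planning scale-up needs to know how many agencies, once approached, take the program on. As written, that reader gets perceptions from people already inside the project and a success statement confined to partners.

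**Working it through.** **1. Definition against indicator.**
- Definition (Implementation Science Framework): uptake, individual or organizational.
- Indicator (Table 3): perceptions of feasibility, acceptability and fit, from focus groups.
- Quantitative Analysis names analyses for reach, effectiveness and maintenance, and none for adoption.
- Qualitative Analysis says all RE-AIM components will also be evaluated qualitatively. For adoption, Table 3 shows nothing for this to supplement.

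Condensing for a journal does not readily explain the gap, since the same table gives counts for Reach.

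**2. The stated result.** Inputs are 11 partnered sites (Phase 2; Table 2) and all sites adopting (Anticipated Findings).
- Adoption among partners = 11 / 11 = 100%. This reproduces the article's statement.
- An exact two-sided 95% interval for 11/11 has lower limit 0.025^(1/11) = 71.5%. It would mean something only if the 11 were a sample from a wider population of agencies, and the article does not present them as one.

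**3. What the wider denominator could do.** Let A be the number of agencies approached, which the article does not give. Adoption among those approached = 11 / A. All values of A below are assumptions.

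| A (assumed) | 11 / A |
|---|---|
| 11 | 100% |
| 12 | 91.7% |
| 15 | 73.3% |
| 20 | 55.0% |
| 30 | 36.7% |

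The table shows only how far the figure depends on A. It is no evidence that any agency declined.

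**4. A count that is already bounded.** With up to 2 workshops at each of 11 sites, the maximum is 11 × 2 = 22 workshops. Workshops delivered out of those planned is a direct uptake measure.

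**5. Who informs the perceptions, and when.**
- Results reports 5 workshop participants, 13 facilitators and 5 organizational leaders: 5 + 13 + 5 = 23 people.
- Five leaders can represent at most 5 / 11 = 45% of sites, and only if each came from a different site.
- Table 4 puts the first set of workshops in 2022, the second set in 2022 to 2023, and the focus groups in 2023. For second-set workshops, views on long-term continuation given then are largely expectations.

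**The case against.** The strongest reply has four parts.

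First, no planned indicator is an 11/11 rate. The sentence sits in the Discussion, and focus-group perceptions could turn out unfavourable. This is right: the plan does not guarantee a favourable adoption finding. A reader might infer that adoption is 100% by construction, but the documents do not support that. A partner could still have failed to recruit or deliver, and Anticipated Findings reports completed workshops as something that happened. Nor does the text say that sites were pre-selected; it says only that they were partners.

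Second, the sentence already names the study's structure and support. That also stands, but it discloses the support, not that the denominator is limited to agencies that had agreed.

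Third, a reader might conclude that sustainability will be no more than a forecast from focus groups held in the same year as the workshops. That goes too far. Table 3 also lists three-time-point surveys and agency tracking, and the tracking is an observed organizational measure. Its missing time window and definition are details that a condensed article may leave to the full protocol. The first workshops preceded the 2023 focus groups, so the same-year point fits only the second set. Textbox 1 asks partly about potential, which is prospective, and about resource use, for which Table 3 has cost ranges.

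Fourth, uptake counts may already be held within the implementation data. If so, the change is easier, but the Adoption row still does not name them.

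**Conclusion.** The point holds for adoption. The only listed indicator does not measure the construct as the article defines it. The only uptake statement is 11 of 11 among trained and coached partners, and it says little about uptake by agencies in general. Strengths and Limitations discusses selection of caregivers and constraints from site mandates, but not how sites came to be in the study.

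The size of any overstatement cannot be computed, because the number approached is not given; the range in the working rests on assumed denominators. If every agency approached agreed, the figure stays at 100% and only the indicator and the wording need attention.

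For maintenance, what remains is a reporting point: focus-group expectations and tracked continuation are different evidence and should not be merged. No participant-level outcome analysis is affected.

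**What to change.** - **Table 3, Adoption row:** add counts from project records: agencies approached and agreeing, facilitators trained and delivering, and workshops delivered out of those planned (at most 22). Keep the focus-group perceptions as the explanation of those counts.
- **Anticipated Findings:** reword to say that all 11 partner sites delivered the workshop with study support.
- **Strengths and Limitations:** add that sites were agencies that had agreed to partner, so the adoption result may not carry over to agencies in general.
- **Maintenance reporting:** present the 2023 focus-group views on continuation as anticipated sustainability, separately from the agency tracking already listed.

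The cost is small. Analysis is still under way, and the counts come from existing records, so no new data collection is needed. The number of agencies approached may have to be reconstructed and should be labelled as such if it is. The adoption figure may then look less favourable than the present wording.
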